### Sample size

Since 2010, analysis of the literature, by synthesizing the results of comparable studies, shows that the ratio between the variability and the clinical difference between healthy subjects and subjects with similar pathologies is generally around 0.5 (for delta/standard deviation or around 2 for standard deviation/delta). With an alpha risk of 5% and a statistical power of 80%, such an effect size leads to a number of 64 subjects per group. With 10% lost to follow-up and/or non-exploitable data, the number of subjects to be recruited in each group is 70. From these elements we therefore set the number of participants to be recruited at 140 subjects: 70 subjects in the patient group and 70 subjects in the healthy control group.

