### Statistical analysis

Both descriptive and comparative analyses will be conducted by accounting for the nature and distribution of the variables. Qualitative variables will be described with frequencies and percentage; quantitative variables with the mean ± SD (standard deviation) or with the median (Inter Quartile Range). For quantitative variables, the Student's *t*-test or the Mann-Whitney U test will be used and for qualitative variables, the chi-square test with, if necessary, the exact calculation of Fisher. The Pearson's coefficient or the Spearman's rho will allow analysis of the correlations. A multivariate analysis will be conducted according to the results of univariate analysis. Regarding the analysis of ERG parameters, after checking the distribution, these will be analyzed *via* generalized estimating equations (GEE) in case of gamma distribution. This is a robust statistical method relevant in the analysis of repeated measures with non-normal response variables (55). Finally, a receiver operating characteristic curve (RoC) will be generated for variables that differed between groups in order to dichotomize the variables of interest and calculate the associated sensitivity and specificity values.

An intermediate data analysis is planned 9 months (mid-term study) after the start of inclusions. The statistical significance level is set at 1% for the interim analysis and 4% for the final analysis. IBM™ SPSS Statistics v23 will be used for the data analysis.

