## Discussion

The aim of the BiMAR study is to compare electrophysiological data measured with ERG between subjects with BD in the euthymic phase and healthy control subjects. Secondarily, we will also study the existing potential relationship between clinical, circadian and neuropsychological phenotypes of patients and electrophysiological data measured with EEG and ERG. To our knowledge, this study will be the first one with these objectives and with a specific methodology in a population of patients with BD.

We hypothesize that electrophysiological data measured with ERG associated with EEG data could help to identify candidate markers. These will then need to be confirmed in subsequent studies with larger samples. If they are validated they could be used in current practice in order to improve the diagnosis and management of patients. Thus, these measures could be integrated in the course of care of patients with BD and contribute to personalized precision psychiatry. One other feature of this research is to use a portable ERG device (Retinaute^®^, BioSerenity), the usability and distribution of which on an outpatient basis would allow good accessibility.

The identification of biomarkers in BD represents a major diagnostic and prognostic challenge in psychiatry. Thus, electrophysiological measurements, in particular with ERG, could be candidate markers of interest in order to be able to improve the diagnosis of patients suffering from BD and in the identification of patient clusters. This will make it possible to improve the diagnosis and to offer earlier and more appropriate therapeutic interventions, thereby reducing the functional impact and the morbidity and mortality of BD.

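### ROC accuracy is to be calculated only for variables that differed, apparently in the same 140 subjects, so sensitivity and specificity as written are biased upward

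*Protocol article*

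**What the plan says.** The last step of the analysis in the protocol article (Statistical analysis) is an ROC curve that "will be generated for variables that differed between groups". Its stated use is "in order to dichotomize the variables of interest and calculate the associated sensitivity and specificity values". The section gives no rule for choosing the cut-off. It sets the significance level at 1% for the interim analysis and 4% for the final one.

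The Sample size section describes a single cohort: "70 subjects in the patient group and 70 subjects in the healthy control group". No second sample is mentioned anywhere in the article.

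The Primary outcomes section lists amplitude and implicit time for four waves (a-wave and b-wave for flash ERG, P50 and N95 for pattern ERG), which makes at least eight primary parameters. The Devices section lists several flash conditions, so the count may be higher.

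The Study design section calls the study exploratory. The aims and the Discussion speak of candidate markers that later studies must confirm. The Discussion also says of identifying such markers: "This will make it possible to improve the diagnosis and to offer earlier and more appropriate therapeutic interventions".

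**The concern.** The section fixes a sequence of select, cut and score, and the only data described for all three steps are the same subjects. Each step favours a high result:

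- **Selection.** A variable reaches the ROC step only if its observed group difference was large enough, so small true effects get through mainly when chance has enlarged them.
- **Cut-off.** A threshold chosen to perform well in these subjects partly fits their noise.
- **Scoring.** Sensitivity and specificity in those same subjects carry both effects.

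The bias follows from the written rule under any cut-off method that uses the same data. Sensitivity and specificity are the figures a reader will use to decide which ERG parameter deserves a confirmatory study and how large that study should be. Inflated values distort both decisions.

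**Working it through.** **Inputs from the protocol article.** Effect size, quoted from Sample size: "is generally around 0.5 (for delta/standard deviation or around 2 for standard deviation/delta". Groups of 64 analysed and 70 recruited. Final significance level 4%. Eight primary parameters (4 flash + 4 pattern).

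**Assumptions, not in the article.** Normal data with equal SD; entry to the ROC step when a two-sided t-test gives p<0.04; cut-off by the Youden index (maximum of sensitivity + specificity − 1), with closest-to-corner as the alternative.

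**1. The plan's own figure.** The article states: "With an alpha risk of 5% and a statistical power of 80%, such an effect size leads to a number of 64 subjects per group". Normal approximation: n = 2(1.960 + 0.842)²/0.5² = 62.8, so 63. The t-test version gives 63.8, so 64, which reproduces the stated number. For 10% loss, 64/0.9 = 71.1 (72) and 64 × 1.1 = 70.4 (71), against the stated 70. The gap is at most 2 per group and does not matter here. Recruiting 70 and losing 10% leaves 63.

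**2. What 0.5 SD can deliver.** The best cut-off lies midway between the two means. Sensitivity = specificity = Φ(0.25) = 0.599, Youden index = 2 × 0.599 − 1 ≈ 0.197, AUC = Φ(0.5/√2) = 0.638.

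**3. Apparent against true accuracy for one flagged variable.** Simulation with 64 per group; the true value is that of the chosen cut-off in the population. The excess is the mean for sensitivity and specificity, in percentage points.

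| True effect (SD) | Apparent sens/spec, Youden | True sens/spec | Excess, Youden | Excess, closest-to-corner |
|---|---|---|---|---|
| 0.8 | 71%/67% | 67%/63% | 4.0 | 2.9 |
| 0.5 | 67%/62% | 62%/57% | 5.5 | 4.3 |
| 0.3 | 66%/61% | 58%/53% | 7.7 | 6.7 |
| 0.2 | 65%/60% | 56%/51% | 9.1 | 8.1 |
| 0 | 65%/60% | 53%/47% | 12.1 | 11.3 |

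In the last row the true sensitivity and specificity sum to 100%, which is no discrimination. With 70 per group and Youden, the excesses are 3.8, 5.1, 7.2, 8.5 and 11.6.

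**4. Share due to the significance gate.** With Youden, 64 per group and no gate, the excess is 4.5 points at 0.5 SD and 7.2 at 0. The gate adds 5.5 − 4.5 = 1.0 point at the planned effect and 12.1 − 7.2 = 4.9 points when nothing is there.

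**5. If the best of eight is highlighted (each 0.5 SD, 63 per group).** Independent parameters: 70%/66% apparent against 61%/58% true, an excess of (70 + 66 − 61 − 58)/2 = 8.5 points each. Correlation 0.5: 68%/65% against 61%/58%, or (68 + 65 − 61 − 58)/2 = 7 points each. Repeated runs place this case at about 7 to 10 points.

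**6. Chance of a false marker.** With no true difference in any of eight independent parameters, P(at least one p<0.04) = 1 − 0.96⁸ = 0.279, about 28%. At correlation 0.5 the simulated figure is about 20%.

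**The case against.** **The study is exploratory.** The article says so, limits its results to candidate markers and leaves confirmation to later work. This stands and limits the harm, since a confirmatory study should catch a false marker. It does not correct the figures this study will report, and those figures decide what goes forward.

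**Internal validation may be planned elsewhere.** The article condenses a fuller protocol, and any analysis plan is not shown. A reader might infer that no validation is planned; the document does not support that. The point rests on the written sequence, not on the silence.

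**A flat figure would overstate the case.** The article plans a curve for every variable that differs and no best-of-eight choice. The 7 to 10 points therefore apply only if one winner is highlighted. At the planned effect, a single variable gives 4 to 6.

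**A null marker would not look like a good test.** About 65%/60% with an AUC near 0.62 reads as weak discrimination, and both figures reach 60% in only 10% to 17% of false positives. It could pass as a candidate marker, not as a usable diagnostic.

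**The patients are not free of comorbidity.** A reader might see a contrast of pure extremes. The criteria exclude other psychiatric and substance use disorders and neurological or retinal disease, but the Discussion expects obesity, diabetes, sleep apnoea and tobacco use and says they will be taken into account. What remains is narrower: the comparison is euthymic patients against screened healthy volunteers, and accuracy figures describe only that.

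**Conclusion.** The point holds in limited form. Followed as written on the one cohort described, the ROC step yields apparent accuracy with upward bias.

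The excess, for sensitivity and specificity each, is about 4 to 6 points per flagged variable at 0.5 SD, 7 to 10 if the best of eight is highlighted, and 12 for a false positive. Across true effects of 0.8 to 0 SD the range is about 3 to 12. With no true effect, about 28% of studies would flag at least one of eight independent parameters, and about 20% at correlation 0.5.

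These sizes rest on normal data with equal SD, a gate at p<0.04 and a cut-off chosen on the data. None of them is a figure from the article. The direction of the bias does not depend on the particular cut-off rule, provided it uses the same data. The group comparison of the ERG parameters is not affected.

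**What to change.** In the Statistical analysis section:

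1. Report the AUC with its 95% CI for every primary ERG parameter, whether or not it differed significantly.
2. Where a cut-off is given, name the rule. Repeat both variable selection and cut-off choice inside each bootstrap sample or each fold of a repeated cross-validation. Report optimism-corrected sensitivity and specificity with CIs beside the apparent values, labelled as such.
3. Describe the figures as discrimination of euthymic bipolar patients from screened healthy volunteers, in line with the candidate-marker wording in the aims and Discussion.

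If a plan not shown already covers item 2, a sentence in the section saying so is enough for that item.

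The cost is a little programming, possibly outside SPSS, and less favourable accuracy figures. No extra participants, visits or measurements are needed.

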## Methods

### Study design

The BiMAR study is an exploratory, open-label and non-randomized comparative moncentric study applied in psychiatry and neuroscience. This research included two groups of adult subjects: a group of patients with BD in the euthymic phase and a group of healthy control subjects. No blinding procedure is planned in this research.

The BiMAR study protocol was reviewed and approved by the French ethics committee (Comité de Protection des Personnes, Ile de France IV) under the reference 2021/60. The study is also registered at Clinicaltrials.gov under the number NCT05161546. All participants in this research will give their written informed consent before the start of any clinical interview, assessment or measurement.

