### Safety monitoring

The participation in the BiMAR study does not involve any particular risk expected. Indeed, this study includes only safe tests and evaluations. Therefore, no research-specific event or adverse effect is expected. The investigators have a good experience in the use of the different devices. Subjects with epilepsy will be excluded from the study because of the repeated light stimulation with the Retinaute^®^ (BioSerenity). We do not expect an effect of the study on the course of BD for patients. However, the natural course of BD may expose patients to the occurrence of an acute decompensation of the illness. In this case, their participation will be stopped and an adapted treatment will be proposed. The investigators will systematically question all participants during various visits in order to look for possible adverse events. The presence or absence of adverse events will be recorded in the study's case report form at each study visit. If an adverse event has occurred from the date of inclusion and throughout the duration of the study, it will be declared without delay according to the French usual reporting's procedure to the concerned health vigilance institution. Anyone with an adverse event will receive treatment appropriate to their condition and will be followed until the event is resolved or until the end of the research. If necessary, the experienced device or test will be stopped for that person.

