### Duration of the study and stopping rules

All participants are volunteers and have given their written consent after receiving information on the objectives and progress of the study. All participants are informed that they are free to accept or decline to participate in this study, just as they are free to terminate their participation at any time during the research. This will not influence the quality of care that will be provided to patients and will not affect their medical care. Note that evaluations do not require interrupting or modifying treatments in progress. The BiMAR study consists of two visits and a 21-day outpatient period. At the end of the second visit, participation in this study will be terminated except for patients who have agreed to participate in the ancillary study who will benefit from a third visit. Given the nature of our research, no particular follow-up is necessary at the end of the participation. Any participant can stop participating in the study at any time and for any reason. The investigator may temporarily or permanently discontinue an individual's participation in this research for any reason which could affect patient safety or would be in the best interests of the patient. In the event of drop-out, the participant is replaced by another of the same category (patient vs. healthy subject).

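### The study is sized for one test at 5%, but the final test runs at 4% to pay for a 9-month group comparison that no stated decision uses

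*Protocol article*

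**What the plan says.** All references are to the protocol article.

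- **Sample size:** with a ratio of difference to standard deviation of about 0.5, a 5% alpha risk and 80% power, "such an effect size leads to a number of 64 subjects per group". The allowance for losses follows: "With 10% lost to follow-up and/or non-exploitable data, the number of subjects to be recruited in each group is 70". The total is set at 140.
- **Statistical analysis:** an intermediate analysis is planned 9 months after inclusions start, and "The statistical significance level is set at 1% for the interim analysis and 4% for the final analysis". The section gives the look no purpose, attaches no action to it and names no recipient.
- **Duration of the study and stopping rules:** the content concerns individuals, for example "Any participant can stop participating in the study at any time and for any reason". It also covers discontinuation of an individual by the investigator and replacement of drop-outs. There is no study-level rule.
- **Study status:** recruitment runs for 18 months to July 2023, with no condition tied to the 9-month analysis.
- **Study design:** "No blinding procedure is planned in this research". **Data management** restricts database access to the investigators.
- **Safety monitoring:** "The participation in the BiMAR study does not involve any particular risk expected". The article therefore gives no safety reason for an early comparison.

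**The concern.** A significance level for the interim means that a hypothesis test between patients and controls is intended, not only a check of progress. The final level is lowered from 5% to 4% to pay for it, yet the sample size is still justified at 5%. The two sections do not match, and the stated 80% power is not the power of the final test as planned.

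An interim test normally earns its cost through a decision such as stopping, continuing or changing the design. This article has a section headed as stopping rules and fixes an alpha split, but the two are not connected. The power is given up without a stated return.

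A second, softer issue is exposure. In an open-label, non-randomised comparison, people who still have subjects to recruit and electroretinogram (ERG) recordings to make could learn halfway through which parameters appear to separate the groups.

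**Working it through.** **Inputs.** From Sample size: d = 0.5, alpha 5%, power 80%, 64 evaluable and 70 recruited per group, 10% loss. From Statistical analysis: 1% interim, 4% final, look at month 9. From Study status: 18 months of recruitment. Assumptions: two-sided tests (sidedness is not stated, but two-sided reproduces the 64) and even accrual, so the information fraction at the look is 9/18 = 0.5. A range of 0.3 to 0.7 is also shown.

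**1. The plan's own figure.** Normal approximation: n = 2(1.960 + 0.842)²/0.5² = 62.8, so 63 per group. The noncentral t distribution gives 64, with power 80.1%. The stated 64 is reproduced at 5%. The recruited 70 less 10% leaves 70 × 0.9 = 63.

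**2. Power at the level actually used.** Normal approximation: power = Φ(d√(n/2) − z), with z = 1.960 at 5% and 2.054 at 4%.

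- n = 64: d√(n/2) = 0.5 × √32 = 2.828. At 5%, Φ(0.868) = 80.7%. At 4%, Φ(0.775) = 78.1%.

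Noncentral t results:

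| Evaluable per group | Power at 5% | Power at 4% |
|---|---|---|
| 63 | 79.5% | 76.7% |
| 64 | 80.1% | 77.4% |
| 70 | 83.6% | 81.1% |

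Moving from 5% to 4% costs about 2.8 points at 64 per group. Holding 80% at the 4% level needs 69 evaluable per group, and 69/0.9 = 76.7, so 77 recruited.

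**3. If an interim rejection counts as success.** Treat the two test statistics as bivariate normal with correlation √0.5 = 0.707, means 2.828 × 0.707 = 2.0 and 2.828, and critical values 2.576 (1%) and 2.054 (4%).

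- Chance of crossing at the interim: Φ(2.0 − 2.576) = 28% (15% to 42% over fractions 0.3 to 0.7).
- Overall power: 78.6% (78.5% to 78.6% over the same range).
- Comparator on the same normal scale, one test at 5%: 80.7%. The net loss is 80.7 − 78.6 = 2.1 points.

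**4. Type I error of the split.** The nominal sum is 1% + 4% = 5%. With the correlation taken into account, the two-look error is 4.5% per parameter at fraction 0.5 (4.3% to 4.7% over 0.3 to 0.7).

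**5. Gap to the stated 80%.** 80 − 78.6 = 1.4 points if an interim rejection counts (64 per group). For the final test alone it is 80 − 77.4 = 2.6 points with 64 per group and 80 − 76.7 = 3.3 with 63.

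**The case against.** The strongest reply is that the split is valid and cheap. It controls type I error, and even conservatively so. The loss is 2 to 3 points in a study that calls itself exploratory and expects later confirmation. ERG is recorded at the inclusion visit and drop-outs are replaced, so the evaluable number may approach 70 per group, where the 4% test has 81.1% power. A purpose and a decision rule may also stand in the full protocol or analysis plan, which are not shown. All of this is fair, and it makes the point modest. It does not remove the mismatch: the article justifies its size at 5%, tests at 4%, and itself allows for 10% lost or unusable data.

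Stronger readings are tempting, but the article does not support them:

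- **That interim results go to the recruiting and recording team.** No recipient is named. Investigator-only database access and the absence of blinding make this possible, even likely, but it is an inference. The team is also unmasked and holds a declared hypothesis from the start, so what the look would add cannot be sized.
- **That the look buys nothing.** Under the design effect it has about a 28% chance of an early positive result. What can be said is that this article states no decision that uses it.
- **That the reported effect will be exaggerated.** Selection on p < 0.01 at mid-term would inflate an estimate only if the study stopped there or reported the interim separately. The article plans neither.
- **That eight null parameters give a 7.7% chance of a false interim signal** (1 − 0.99⁸). This is a multiplicity figure that assumes independence between measures from the same recordings. It is not a consequence of the interim look.

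**Conclusion.** The concern holds in a limited form. The sample size is computed for a single 5% test, while the final test is set at 4% to fund a comparison that no stated stopping or continuation decision uses. With 63 to 64 evaluable per group, the final test has about 77% power rather than 80%, or about 78.6% overall (at 64) if an interim rejection counts. The shortfall of roughly 1.5 to 3 points disappears only if at least 69 of the 70 recruited per group are evaluable.

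These figures rest on d = 0.5, two-sided tests of one parameter and, for the overall figure, roughly even accrual; the result barely moves over information fractions of 0.3 to 0.7. There is no type I error fault. Knowledge of a mid-study group comparison in an unmasked study is a risk worth closing off, not a demonstrated bias.

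**What to change.** Preferred: in the Statistical analysis section, limit the 9-month analysis to recruitment, recording quality, missing data and adverse events, with no patient-versus-control comparison of ERG or EEG. Delete the 1%/4% split and test once at the end at 5%. Power returns to 80.1% with 64 evaluable per group (79.5% with 63), in line with the Sample size section.

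If the comparison is kept:

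- state in the section on duration and stopping rules that the study continues to 140 whatever the interim result;
- keep the result from those who recruit or record, and name who receives it;
- restate the final-test power in the Sample size section as about 77% at the 4% level with 64 per group.

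Either route changes wording only. The preferred route costs the early group result. The alternative keeps that result but requires accepting the lower power openly.

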### Study aims and hypotheses

The aim of the BiMAR study is to analyse the differences in the electrophysiological data measured with ERG pattern (PERG) and flash (fERG) between a group of subjects with BD in euthymic phase and a group of healthy control subjects.

Secondarily, we also want to:
Compare combined electrophysiological measurements with ERG and EEG between the two groups.Identify relations between clinical, neuropsychological and circadian phenotypes in patients with BD and electrophysiological measurements measured with ERG and EEG.

Our main hypothesis is that differences exist in the ERG and EEG measurements between subjects with BD and healthy subjects. Those differences could be identified as candidate markers for BD which, if confirmed in later studies, could be used in current practice to guide the management of patients with BD.

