## Study status

Recruitment of participants began in January 2022 and will continue over a period of 18 months until July 2023. The latest data collection is scheduled for the end of July 2023, after the last visit of the last included participant. We plan to disseminate our findings through oral and poster presentations at national and international conferences, as well as through international publications.

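### The 1% interim and 4% final levels are a valid but conservative split of 5%; allowing for the correlation between the looks would recover about 1.5 points of power per ERG parameter

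*Protocol article*

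**What the plan says.** The Statistical analysis section of the protocol article says: "An intermediate data analysis is planned 9 months (mid-term study) after the start of inclusions". It then fixes the thresholds: "The statistical significance level is set at 1% for the interim analysis and 4% for the final analysis". It gives no derivation, names no boundary and does not say that the interim can stop the study.

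The Sample size section plans "With an alpha risk of 5% and a statistical power of 80" per cent, takes a difference that "is generally around 0.5 (for delta/standard deviation", and concludes that "such an effect size leads to a number of 64 subjects per group". It does not mention the interim. On recruitment, the Study status section says it "will continue over a period of 18 months until July 2023", so nine months is the calendar midpoint.

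**The concern.** The two levels sum to exactly 5%, which suggests that the final level was set by subtraction, although the article does not say so. Adding levels gives the overall error exactly only if the two tests can never reject together. A final analysis ordinarily includes the interim participants, and nothing here says otherwise. The two statistics are then positively correlated, joint rejections are counted twice, and the procedure spends less than 5%. The unspent part could go to the final test of each primary ERG parameter.

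What is at stake is a small amount of power at an unchanged sample size. That has some value because 64 per group gives 80% only at a 5% level, while the final test is run at 4%.

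**Working it through.** **Inputs**
- Planned alpha 5%, power 80%, standardised difference 0.5, 64 evaluable per group: Sample size section.
- Interim level 1%, final level 4%, interim at 9 months: Statistical analysis section.
- Recruitment over 18 months: Study status section. With even accrual (an assumption) the information fraction is t = 9/18 = 0.5. The range 0.2 to 0.8 is shown because the plan fixes a date, not a number of participants.
- Two-sided tests: not stated, but they fit the undirected hypothesis ("Our main hypothesis is that differences exist in the ERG and EEG measurements") and reproduce the plan's sample size.

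**Step 1: the plan's own figure.** For a two-sided t-test with n per group, the noncentrality is 0.5 × √(n/2) on 2n − 2 degrees of freedom. At n = 64 this is 0.5 × √32 = 2.83, and power at 5% is 80.1%. At n = 63 it is 79.5%. The stated 64 is reproduced.

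**Step 2: error spent by 1% then 4%, one parameter.** The critical values are 2.576 and 2.054. Under the null hypothesis the interim and final statistics are approximately bivariate normal with correlation √t, which is √0.5 = 0.71 at half information. The overall error is 1 − P(|Z1| < 2.576 and |Z2| < 2.054).

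At t = 0.5 this is 4.51%; a simulation of 4 million draws gave 4.52%. The gap of 5.00 − 4.51 = 0.49 points is the probability that both looks reject. If the two tests were independent, the figure would be 1 − 0.99 × 0.96 = 4.96%, so nearly all of the gap comes from the correlation.

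**Step 3: final level that uses the full 5%.** Keep 1% at the interim and solve for the final level that makes the overall error 5%. Power is for the final t-test with 64 per group; the gain is over 4%.

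| Information fraction | Error with 1% then 4% | Final level for 5% overall | Power at that level | Gain (points) |
|---|---|---|---|---|
| 0.2 | 4.80% | 4.21% | 78.0% | 0.6 |
| 0.3 | 4.71% | 4.30% | 78.3% | 0.9 |
| 0.5 | 4.51% | 4.52% | 78.9% | 1.5 |
| 0.7 | 4.27% | 4.77% | 79.6% | 2.2 |
| 0.8 | 4.15% | 4.89% | 79.9% | 2.5 |

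**Step 4: size at half information.** Final-test power with 64 per group is 77.4% at 4%, 78.9% at 4.52% and 80.1% at 5%. The adjusted level therefore recovers 1.5 of the 2.7 to 2.8 points (depending on rounding) lost by testing at 4%. Expressed as sample size, 80% power needs 69 per group at 4% and 66 at 4.52%.

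**Step 5: why 4.52% should not be fixed in advance.** If 4.52% were written into the plan and the interim came at t = 0.3, the overall error for one parameter would be 5.2%.

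**The case against.** The strongest reply is that nothing in the plan is wrong. A 1% + 4% split controls the error of each test at or below 5% for any interim timing, any correlation between looks and any choice of test. The article leaves that choice open between the t-test, Mann-Whitney and GEE, and fixes the interim by calendar. It never claims to spend exactly 5%. That reply stands, and it is why this is an improvement and not an error. The freedom from assumptions is a real merit of the present rule. Against that, the square-root-of-information correlation holds approximately for all three tests, and setting the level from actual counts removes the dependence on timing.

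A reader might go further and infer that the study's true overall error is 4.5% and that the plan is too strict as a whole. The documents do not support this. The 4.5% applies to one parameter. The Primary outcomes section lists eight main parameters (amplitude and implicit time of the a-wave, b-wave, P50 and N95), and the article describes no adjustment across them. As an illustration only, eight independent tests at 4% would give 1 − 0.96^8 = 28% at the final analysis alone. The real parameters are correlated, so that figure is not an estimate, but the study-wide error cannot be read as 4.5%.

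It is also fair to say that the larger matter is the sizing at 5% against a final test at 4%. The change proposed here narrows that gap without closing it.

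**Conclusion.** The point holds as a low-cost gain in efficiency. For each ERG parameter taken alone, the two stated levels spend about 4.5% of the planned 5%, and the final test gives up about 1.5 points of power with 64 per group (77.4% against 78.9%). This rests on two-sided testing, a standardised difference of 0.5, a final analysis that contains the interim participants, the joint-normal approximation, and even accrual so that nine months is half the information. An earlier interim shrinks the gain to 0.6 to 0.9 points (t = 0.2 to 0.3); a later one raises it to about 2.2 to 2.5 (t = 0.7 to 0.8). At every fraction examined, the allowable final level exceeds 4%.

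**What to change.** If the 1% interim comparison is kept, replace the fixed 4% in the Statistical analysis section with a rule: the final level is the one that gives a 5% two-sided error per parameter across both looks, calculated from the number of participants actually included at the interim relative to the final analysis. For orientation, this is 4.2% at an information fraction of 0.2, 4.3% at 0.3, 4.5% at 0.5 and 4.8% at 0.7. State the rule, and do not write 4.5% into the plan.

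The cost is one sentence, a short recalculation that needs no outcome data, and reliance on the joint-normal approximation. No participants are added. The change does not deal with multiplicity across the eight primary ERG parameters, and final-test power with 64 per group remains slightly below the stated 80%.
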